### Population

Patients will be recruited in acupuncture clinics in the Beijing Hospital of Traditional Chinese Medicine Affiliated to Capital Medical University, the Beijing Huairou District Hospital of Traditional Chinese Medicine, and the Dongzhimen Hospital Affiliated to Beijing University of Chinese Medicine, with a target sample size of 164 subjects. The trial will be executed from January 2014 to December 2015.

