### Randomization and blinding

This is a block randomized single blind 2 × 2 factorial design. Randomization is to be conducted by a statistics specialist who will have no contact with the participants. Random numbers with block randomization are generated with SAS software (SAS Institute, Inc., Cary, NC, USA). Participants will be allocated to one of the four groups at a ratio of 1:1:1:1. The research coordinator, who will not be involved with data collection, will inform the acupuncturist of the treatment assignment via the telephone.

The patients, data collection staff, and data analysts will be blinded during the study period. Acupuncturists are not blinded to the treatments they deliver due to the nature of the intervention. During the intervention, the acupuncturist and personnel who collect data will be segregated immediately after the start of treatment and are instructed not to exchange information with each other.

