### Sample Size

According to the previous pilot study [4],an average 20-point reduction on the VAS scores relating to shoulder pain has a clinically significant difference, and percentages of responders for the primary endpoint are verum 65%, sham 24%. The following formula is used for a four-group trial [11]:

$$n=\frac{2\lambda }{{\left(2\mathrm{si}n^{‒1}\sqrt{P_{\text{max}}}‒2\mathrm{si}n^{‒1}P_{\text{min}}\right)}^{2}}$$

Based on 0.9 power to detect a significant difference (α = 0.05,ν = 4-1 = 3,λ =14.17), the required sample size is 34 patients in each group. Allowing for 20% attrition, we should recruit 164 patients, with 41 in each group.

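### Recruiting 41 per group does not leave the stated 34 after the stated 20% attrition; 41 covers a loss of about 17%

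*Protocol article*

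**What the plan says.** The Sample Size section of the protocol article names a design power ("Based on 0.9 power to detect a significant difference") and the constants "α = 0.05,ν = 4-1 = 3,λ =14.17", and concludes that "the required sample size is 34 patients in each group". The next sentence sets the recruitment target: "Allowing for 20% attrition, we should recruit 164 patients, with 41 in each group".

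The Population section repeats the total ("with a target sample size of 164 subjects"), as does the Abstract. Allocation is equal across four arms: "Participants will be allocated to one of the four groups at a ratio of 1:1:1:1". The article does not show how 34 became 41, and nowhere does it define the 20% as anything other than attrition.

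**The concern.** An attrition rate is ordinarily a fraction of those recruited, so the number recruited must be the number required divided by the fraction retained. Adding 20% of the required number gives a smaller target, and a 20% loss then takes the group below the requirement.

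The required number, the attrition rate and the recruitment target stand in two consecutive sentences, and the target does not satisfy the other two. A reader would take it that the trial can lose one patient in five and still have the number its power statement rests on. It cannot.

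**Working it through.** **Inputs, all from the protocol article**
- Required per group: 34, so 34 × 4 = 136 in total (Sample Size).
- Attrition: 20% (Sample Size).
- Recruitment: 41 per group, 164 in total (Sample Size; total repeated in Population).
- Four groups, equal allocation (Randomization and blinding).
- α = 0.05, 3 degrees of freedom, λ = 14.17, power 0.9 (Sample Size).

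**Step 1. Reproduce the stated target.**
- Multiplying: 34 × (1 + 0.20) = 40.8, rounded up to 41; 41 × 4 = 164. This matches both stated figures exactly.
- Dividing: 34/(1 − 0.20) = 42.5, rounded up to 43; 43 × 4 = 172. This does not match.

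Multiplication by 1.2 is therefore the likely route, but it is an inference. Steps 2 and 3 do not depend on it.

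**Step 2. Apply the stated attrition to the stated target.**
- Per group: 41 × 0.80 = 32.8, against 34 required. Shortfall 1.2.
- In total: 164 × 0.80 = 131.2, against 136 required. Shortfall 4.8.

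**Step 3. Find the attrition that 41 per group can absorb.**
- 1 − 34/41 = 0.171, or about 17%.

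**Step 4. Gap in recruitment.**
- 43 − 41 = 2 per group; 172 − 164 = 8 in total; 8/164 = 4.9%.

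**Step 5. Effect on power, taking 34 as given.** With other inputs fixed, the noncentrality parameter is proportional to the group size. The 5% critical value of chi-square on 3 degrees of freedom is 7.815.

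| Evaluable per group | λ | Power |
|---|---|---|
| 34 | 14.17 | 90.0% |
| 33 | 14.17 × 33/34 = 13.75 | 89.0% |
| 32.8 | 14.17 × 32.8/34 = 13.67 | 88.8% |

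The attrition step alone costs 90.0 − 88.8 = 1.2 percentage points.

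**Step 6. Does the size of the loss depend on accepting 34?** As a sensitivity check, use the responder rates of 65% and 24% in the arcsine formula. This assumes a square root on both proportions, whereas the formula as it appears in the article has none on the smaller one. The difference is 2·arcsin√0.65 − 2·arcsin√0.24 = 0.8515, and λ = n × 0.8515²/2.
- n = 34: λ = 12.33, power 85.1%.
- n = 32.8: λ = 11.89, power 83.7%.

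The loss from attrition is 1.4 points, much the same. The lower starting level on this basis comes from the 34, not from the allowance.

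**The case against.** The strongest reply is that this hardly matters. The shortfall is 1.2 evaluable patients per group and about one point of power, and no conclusion of the trial is likely to turn on it. That stands. It limits the point to a correction of the text and gives no ground for enlarging a trial that is already recruiting.

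It can also be said that the protocol never states that it multiplied by 1.2. That is true, and the step is described here only as an inference. The shortfall remains however 41 was reached.

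One might defend the figure by reading the 20% as a share of the 34 rather than of those recruited. The 7 extra patients would then be about 20% of 34. The article gives no such definition, and losing 7 of 41 is 17% attrition.

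Two stronger readings are tempting, and neither belongs to this point:
- A reader might infer that the attrition error drops power from 90% to about 84%. It does not. On the basis that gives 84%, power is already 85.1% at 34, so about 5 of the 6 points come from the base figure. Nor is this the power of the planned analysis: Data analysis specifies a two-factor ANOVA with an interaction term, and the primary outcome is pain intensity on the VAS. The responder comparison serves only to size the trial.
- A reader might infer that the trial needs 50 per group, or 200. That combines this point with a different base of 40, since 40/0.8 = 50. The base of 40 depends on reading a square root into the formula where none appears. It is a question about the 34 and should be settled separately.

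**Conclusion.** The attrition statement is wrong as written. At the protocol's own 20% loss, 41 per group leaves 32.8, not 34; the figure consistent with 34 and 20% is 43 per group, 172 in total. The target is short by 2 per group and 8 overall, and 164 covers about 17% attrition.

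The effect on power is about one percentage point, to about 89% if 34 is accepted as giving 90%. This rests on two assumptions: that the 20% is a fraction of those recruited, and that 34 means patients with usable outcome data, as an allowance for attrition implies. The article does not restrict the analysis to completers. The point takes no position on whether 34 is itself correct. It should be corrected because the stated sample-size margin is not what the trial has, and the correction is cheap.

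**What to change.** Keep 164 and correct the one sentence in Sample Size, in either of two ways:
- State that 41 per group allows for about 17% attrition if 34 per group are to be evaluable.
- Keep the 20%, and state that it leaves about 33 evaluable per group with power slightly under 0.9 (about 89% if 34 is taken as giving 90%).

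Either way, state that the percentage refers to patients recruited. If the base of 34 is revised for other reasons, recalculate the sentence from the new base by dividing by 0.8.

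The cost is one sentence and a slightly less favourable attrition tolerance or power. No further enrolment and no change in trial procedures is needed.

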### Data analysis

Statisticians who are independent from the research team will analyze data in accordance with a 2 × 2 randomized factorial study design. Every analysis is to be conducted using the software of SPSS 12.0. The statistical model includes two fixed factors (local acupoints and distal acupoints). Interaction is to be evaluated by the interaction term in the analysis of variance (ANOVA) model and visual assessment of profile plots.

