**Methods/Design:**

This is a multicenter, single blind, factorial randomized controlled clinical trial. A total of 164 participants will be randomly allocated to four different groups: Group A will receive acupuncture at local acupoints in combination with distal acupoint. Group B will receive acupuncture at local acupoints in combination with distal non-acupoint. Group C will receive acupuncture at local non-acupoints in combination with distal acupoint. Group D will receive acupuncture at local non-acupoints in combination with distal non-acupoint. Each group will receive 12 treatments of acupuncture one to three times per week for six weeks in total. The primary outcome is shoulder pain intensity, which is graded using a 100 -mm Visual Analogue Scale. The assessment is at baseline (before treatment initiation), 6 weeks after the first acupuncture, 10 weeks after the first acupuncture and 18 weeks after the first acupuncture.

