### Recruitment of participants

Two strategies will be used to recruit participants with CSP. One is to recruit participants in outpatient clinics from the three hospitals mentioned above. The other is to show recruitment posters outside the clinics. The posters will contain brief introductions about the population needed, the free acupuncture treatments offered to eligible participants, and the contact information of the researcher. Screening forms will be completed by interested patients, which will be conducted via a face-to-face interview and assessment with a researcher at one of the hospital sites prior to randomization.

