### Inclusion criteria

Patients who meet all of the following conditions will be considered for enrollment. The inclusion criteria are as follows: aged between 25 and 65 years (either sex); present with a primary complaint of shoulder pain with one-sided shoulder pain for at least six weeks and up to two years; a pain score of 50 mm or more on a 100 -mm visual analogue scale (VAS); plain radiography is normal, but osteoporosis or a calcification shadow may be present; individuals had not received acupuncture in the preceding month; and a signed informed consent form.

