### Primary outcome measures

Shoulder pain intensity will be graded using a 100-mm Visual Analogue Scale (VAS) by patients themselves, with 0 representing ‘no pain at all’ and 100 mm representing ‘the most intense pain imaginable’ [4]. The assessment is at baseline (before treatment initiation), 6 weeks after the first acupuncture, 10 weeks after the first acupuncture and 18 weeks after the first acupuncture.

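### The stated two-factor ANOVA names no baseline covariate although every continuous efficacy outcome is measured at baseline, so precision is given up at almost no saving

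*Protocol article*

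**What the plan says.** The Data analysis section describes a 2 × 2 factorial analysis: "The statistical model includes two fixed factors (local acupoints and distal acupoints"). It continues: "Interaction is to be evaluated by the interaction term in the analysis of variance (ANOVA) model and visual assessment of profile plots". The named terms are therefore local, distal and local × distal. No covariate is named, and the section does not say whether the response is the follow-up score or the change from baseline.

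The primary outcome is continuous: "Shoulder pain intensity will be graded using a 100-mm Visual Analogue Scale (VAS) by patients themselves". Its timing is given as "The assessment is at baseline (before treatment initiation), 6 weeks after the first acupuncture", followed by 10 and 18 weeks. Secondary outcome measures gives the same baseline and follow-up times for the Constant-Murley score and the SF-36. The Treatment Credibility Scale is taken only after the 6-week course and has no baseline.

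Two further statements bear on the point. Entry requires "a pain score of 50 mm or more on a 100 -mm visual analogue scale (VAS"). Recruitment is at three hospitals, while Randomization and blinding says "Random numbers with block randomization are generated with SAS software" and mentions no stratification by hospital.

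**The concern.** A patient's pain before treatment usually predicts some of that patient's pain afterwards. In a model containing only the randomised factors and their interaction, that predictable part stays in the error term. Chance differences in baseline pain between groups then add noise to the estimates, where a covariate would remove it.

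The trial's question makes precision valuable. The Background and Discussion ask whether local plus distal points do better than either alone. That is answered by differences between single cells and by the interaction, which are estimated less precisely than the main effects. The data needed to sharpen them are already being collected.

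**Working it through.** The documents give no VAS standard deviation, no correlation and no standard error, so there is no figure of the plan's own to reproduce on this point. What follows is a range under stated assumptions.

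**Inputs**
- Planned evaluable patients: 34 per group, so 4 × 34 = 136 (Sample Size).
- Model terms: local, distal, local × distal (Data analysis), leaving 136 − 4 = 132 residual degrees of freedom.
- ρ, the within-group correlation of baseline with follow-up: not given; assumed 0.3 to 0.6.
- Follow-up SD: not given; 25 mm assumed for illustration only.

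**1. Response is the follow-up score.** Adding the baseline value multiplies residual variance by 1−ρ² and every standard error by √(1−ρ²). The equivalent sample size is 136/(1−ρ²).

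| ρ (assumed) | 1−ρ² | √(1−ρ²) | 136 patients act like |
|---|---|---|---|
| 0.3 | 0.91 | 0.954 | 149 |
| 0.4 | 0.84 | 0.917 | 162 |
| 0.5 | 0.75 | 0.866 | 181 |
| 0.6 | 0.64 | 0.800 | 212 |

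The 50 mm entry threshold narrows the spread of baseline VAS and tends to lower ρ, so the upper rows are the less likely ones for the primary outcome. At ρ = 0.2 the variance factor is 0.96 and standard errors shrink by only 2%.

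**2. On the VAS scale (SD 25 mm assumed, N = 136).**
- Main effect: 2·SD/√N = 50/11.66 = 4.29 mm; adjusted, 4.09 mm (ρ = 0.3) to 3.43 mm (ρ = 0.6).
- Single-cell contrast, such as A against B: SD·√(2/34) = 25 × 0.2425 = 6.06 mm; adjusted, 5.78 to 4.85 mm.
- Interaction: 4·SD/√N = 100/11.66 = 8.57 mm; adjusted, 8.18 to 6.86 mm.

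For an assumed 10 mm main effect (two-sided 5%, normal approximation), power rises from 64.5% to 68.6% at ρ = 0.3 and 83.0% at ρ = 0.6. These levels depend on the assumed SD and effect; the proportional reduction in standard error depends only on ρ.

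**3. Response is change from baseline.** Let k be the baseline SD divided by the follow-up SD. In units of follow-up variance, the change score has variance 1 + k² − 2ρk and ANCOVA has 1 − ρ². The difference is

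(1 + k² − 2ρk) − (1 − ρ²) = (k − ρ)²,

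which is never negative. With k = 1, the change-score variance is 1.40 against 0.91 at ρ = 0.3 (54% larger) and 0.80 against 0.64 at ρ = 0.6 (25% larger). The entry threshold may make k less than 1, which narrows the gap as k approaches ρ; at k = ρ the two are equal.

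**4. Cost.** One baseline covariate uses 1 of 132 residual degrees of freedom, about 1/132 = 0.8% in variance. It pays once ρ² exceeds about 0.008, that is, ρ above roughly 0.09.

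**The case against.** The strongest objection is one of scope. This is a journal article with a short analysis section, and saying that a model includes two factors does not say that it excludes everything else; covariates may be listed in a fuller document. That is fair, and it means the article cannot be read as forbidding adjustment. But it names the method, the factors and the interaction, and an analyst following that text would run an unadjusted ANOVA. The point therefore concerns a stated model for which a better one is available.

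A second objection is that the response might be change from baseline, since Sample Size speaks of a 20-point reduction. The figures in the table would then not apply. The recommendation survives, because ANCOVA has residual variance no larger than either alternative, apart from the single degree of freedom.

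A third is that the gain is assumed. This stands: neither ρ nor the SD is in the protocol, and at ρ = 0.3 standard errors fall by only about 5%.

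Three stronger readings are tempting and are not supported:
- **That the unadjusted results would be biased.** Randomisation keeps the estimates unbiased, and their confidence intervals already allow for chance imbalance. The main effects also compare margins of about 68 patients each (2 × 34), not single cells.
- **That omitting hospital loses precision.** The trial is multicentre, but no between-hospital variance is given and no stratification by hospital is stated, so the effect of leaving it out cannot be computed.
- **That the omission worsens a shortfall in stated power.** Sample Size rests on a four-group comparison of responder proportions, which does not give the power of a two-factor analysis of a continuous score. How that section reaches its number is a separate matter.

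**Conclusion.** The point holds as one of efficiency. The stated model contains the two factors and their interaction and names no baseline covariate, although VAS, Constant-Murley score and SF-36 all have baseline values.

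The size is conditional: for a follow-up-score response and an assumed ρ between 0.3 and 0.6, baseline adjustment removes 9% to 36% of residual variance, with the VAS probably near the lower figure. This assumes a roughly linear relation with a common slope across groups. For a change-score response the gain depends also on the ratio of the two SDs, but is never negative apart from the small degrees-of-freedom cost. Validity is not in question.

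**What to change.** In Data analysis, replace the ANOVA by an ANCOVA, at each follow-up time:

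follow-up outcome ~ local + distal + local × distal + baseline value of the same outcome

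Use this form for VAS, Constant-Murley score and SF-36, and state that the response is the follow-up score. The interaction is already planned and stays. The Treatment Credibility Scale has no baseline and is unaffected.

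The cost is wording and one degree of freedom per model; no new data or patients are needed. The article describes the trial as recruiting and the data analysts as blinded, so the covariate can be fixed before results are known. If a fuller protocol or analysis plan already specifies it, the article's text need only be aligned with that.

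Hospital may be added as a fixed effect for two further degrees of freedom. This is good practice, particularly if randomisation is done by hospital, but it is optional on the evidence here.

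### The ANOVA described has no patient or visit term, although outcomes are measured at three follow-up visits and 20% attrition is allowed for; a mixed model over all visits would use the data better

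*Protocol article*

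**What the plan says.** The Data analysis section of the protocol article describes one model: "The statistical model includes two fixed factors (local acupoints and distal acupoints"). It adds that interaction is assessed through the interaction term of an analysis of variance and through profile plots. It names no term for patient, visit or baseline value.

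Under Primary outcome measures, VAS pain is recorded at baseline and "6 weeks after the first acupuncture, 10 weeks after the first acupuncture and 18 weeks after the first acupuncture". Under Secondary outcome measures, the Constant-Murley score and SF-36 follow the same schedule.

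The Sample Size section provides for incomplete follow-up: "Allowing for 20% attrition, we should recruit 164 patients, with 41 in each group".

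The article does not say which visit the model is applied to, which patients are analysed, or how missing values are treated.

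**The concern.** An ANOVA with two between-patient factors takes one value per patient. Applied to week 10 or week 18, it has no use for a patient without that value and takes nothing from that patient's week 6 measurement. Reading it as a classical repeated-measures ANOVA does not help, because that analysis needs every visit and also omits incomplete patients. Only imputation or a likelihood-based model would avoid this, and neither is described.

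Treatment ends at week 6 and follow-up runs to week 18, so some patients lost late will have a week 6 pain score. If patients in more pain leave more often, and the study hypothesis is right, more of them will be in the non-acupoint arms. The patients who remain in those arms then look better than the arm as a whole, and the local and distal effects at later visits are understated. Even if loss is unrelated to pain, the week 6 values of those who leave go unused, which costs some precision.

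**Working it through.** **Numbers remaining.** The attrition step is 34 × 1.2 = 40.8, rounded to 41 per group, and 4 × 41 = 164. This reproduces the stated total. If 20% are lost, 164 × 0.8 = 131.2 patients remain, or 32.8 per group.

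**Assumptions, none of them in the protocol.** VAS has SD 25 mm. The correlation r between week 6 and week 18 is 0.5 to 0.7. The true local effect is 12 mm. All loss occurs after week 6, totals 20%, and depends only on week 6 pain through a logistic rule that is the same in every arm.

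**Loss unrelated to pain.** A main effect compares half the patients with the other half, so the standard error among completers is 2 × SD / √131.2 = 50 / 11.45 = 4.37 mm. Then 12 / 4.37 = 2.75, and power is Φ(2.75 − 1.96) = Φ(0.79), about 78%. The estimate is unbiased. Using the week 6 values multiplies the variance by 1 − 0.2r²:

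- r = 0.5: factor 0.95, SE 4.25 mm, 12 / 4.25 = 2.82, power Φ(0.86), about 80%.
- r = 0.7: factor 0.902, SE 4.15 mm, 12 / 4.15 = 2.89, power about 82%.

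The cost of ignoring the earlier visit is therefore about 2 to 4 points of power.

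**Loss related to week 6 pain.** The table gives simulation results (4,000 trials per setting) for the week 18 completer ANOVA at r = 0.7. The odds ratio per SD is exp(25 × log-odds).

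| Log-odds of loss per mm | Odds ratio per 25 mm | ANOVA estimate (truth 12 mm) | Shortfall |
|---|---|---|---|
| 0 | 1.0 | 11.9 mm | none beyond simulation error |
| 0.02 | 1.6 | 11.6 mm | 0.4 / 12 = 3% |
| 0.04 | 2.7 | 11.0 mm | 1.0 / 12 = 8% |
| 0.06 | 4.5 | 10.4 mm | 1.6 / 12 = 13% |

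At r = 0.5 the shortfall is smaller, for example 11.3 mm (0.7 / 12 = 6%) at 0.04. At log-odds 0.04 to 0.06, loss is 16–17% with local acupoints and 23–24% without, and ANOVA power is 70% to 75%. A likelihood estimator that also uses week 6 returns about 12.0 mm with power 80% to 82%.

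**A second set of assumptions.** With SD 20 mm, local and distal effects of 10 mm each, 20% loss and correlations of 0.4 to 0.8, each effect shrinks by:

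- 0.1–0.4 mm when the odds of loss rise 1.35 times per 10 mm of week 6 pain,
- 0.5–1.1 mm when they rise 1.8 times,
- 0.9–1.9 mm when they rise 2.7 times.

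That is about 1% to 19%. The top of the range comes from a steeper dropout rule (log-odds 0.10 per mm) than any in the table.

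**Set against sampling error.** The largest shortfall in the table is 1.6 / 4.37 = 0.37 standard errors, and it is toward no effect.

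**No true effect.** When the dropout rule is the same in all arms, the completer ANOVA shows about zero bias, and 5.6% of simulated trials reject against a nominal 5%.

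**The case against.** A reader might infer that the plan commits to a single-visit ANOVA and discards every patient who misses that visit. The article does not say so. It says what the model includes, which leaves room for further terms. It names no visit and is silent on the analysis set and on missing data. An article may leave those details to the full protocol or the analysis plan, so the silence is not itself a fault. This part of the objection stands.

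A reader might also infer that the trial's estimates will be biased. That does not follow either. The 20% is a planning margin with no stated timing, cause or pattern by arm, and nothing in the article says that patients who do not improve will leave. The simulation also favours the mixed model: every lost patient has a week 6 value, and loss depends only on that value, which is the condition under which a likelihood analysis is unbiased. Loss driven by later, unobserved pain would bias both methods and was not examined. At week 6 the set-up produces no bias at all, and since no primary visit is named, the primary comparison might be unaffected.

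What remains is that the article does name a model, that this model does not match three repeated measurements, and that its two ordinary readings both leave out incomplete patients. A better method is available from data already planned.

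**Conclusion.** The point holds as a modest and conditional one. The model described has no patient or visit term and, run that way without imputation, makes incomplete use of the follow-up data. Under random loss there is no bias and about 2 to 4 points of power are lost. If loss after week 6 rises with pain, later effects are understated by about 3% to 13% for log-odds of 0.02 to 0.06 per mm, with SD 25 mm and a true effect of 12 mm. That is less than half a standard error. The harm is attenuation and some lost power, not a spurious effect, provided the dropout rule does not differ between arms. Every one of these sizes rests on assumptions from outside the protocol.

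**What to change.** Analyse VAS, Constant-Murley score and SF-36 with a linear mixed model on all randomised patients who have any post-baseline value:

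- weeks 6, 10 and 18 as repeated measures, with an unstructured within-patient covariance;
- visit, local, distal, local × distal, and the products of these treatment terms with visit as fixed effects;
- the baseline value, which is already collected, as a covariate.

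Take the factorial contrasts from this model at one visit named in advance, and report losses by arm and visit.

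The cost is a change of wording and slightly more analysis work; no further patients or measurements are needed. The sponsor should confirm that the software release named in the article can fit the model. The model relies on missingness depending only on observed values, and it does not recover the outcomes of patients lost before week 6.
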